#### Outcome measures

Primary outcome: Time to achieve bi-directional block(secs) . This is defined as the time from the first lesion to the time that consistent (> one minute) bidirectional block is achieved.

Total RF energy required for the whole procedure (sec), and total energy required for ablation (power x ablation time in secs).

Secondary outcomes: complications during initial hospitalisation and during six month follow up, isthmus re-conduction during the 30 minute waiting period, total procedure time, procedural cost, fluoroscopy time,

radiation exposure, total radiofrequency energy delivered, and long term success rate (freedom from AFL episodes of >30seconds duration following discontinuation of anti-arrhythmic medication), isthmus re-conduction at repeat procedure.

### Sample Size

Previous studies have focussed on number of RF lesions (mean typically 12 – 19) and total procedural time (mean typically 100-150mins), along with fluoroscopy time (mean typically 2-10 mins). No local data is available to guide timings for bidirectional block using different catheter technologies and mapping systems. Therefore based on prior publications, a sample size of 120 patients is sufficient for this feasibility study i.e. 30 patients in each group.

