## **HYPOTHESES**

We hypothesise that:

1. The use of either contact force or ECI will result in lower procedure time, reduced RF requirements and improved outcomes compared to the conventional approach.
2. There would be no difference in outcome measures between contact and ECI, as both provide the operator with information about the tissue catheter interface.

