## **STUDY DESIGN**

In order to examine these hypotheses we aim to perform a multicentre prospective, randomised study comparing RF energy time, procedure duration and outcome of catheter ablation of AFL between non-contact 3D guided ablation (i.e. blinded to contact or ECI sensing), contact force sensing and the assessment of ECI. Patients will be followed up for 6 months post procedure.

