### Statistical methods

Continuous variables will be checked for normality. If they are normally distributed the results will be expressed as mean  $\pm$  SD and compared by Student's t-test or ANOVA. If they are skewed the results will be expressed as median and interquartile range, and compared using the Mann Whitney U test. A chi-squared test will be used to compare categorical variables. A p value <0.05 will be considered statistically significant. Alternative statistical methods and additional analyses will be conducted as deemed appropriate.

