#### **Expected value of results**

There is evidence that catheter ablation for AFL is superior to medical therapy both in terms of clinical and economic outcomes, and AFL ablation is now considered as routine practice. Further, what is becoming evident is that knowledge of tissue catheter interaction reduces procedure time and can improve outcomes. What is unclear is whether the individual differences between contact technologies offer specific clinical advantages, and this trial will provide insight into this. In addition, information about the catheter tissue interface may make the procedures safer as high forces that can potentially traumatise myocardium can be avoided. Finally, the ability to tell that the catheter is delivering effective energy to tissue can potentially shorten procedure times allowing more patients to be treated. The results are potentially applicable to catheter ablation of atrial fibrillation and ventricular tachycardia.

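### The sample size is justified only as a feasibility study, yet the protocol examines comparative hypotheses at p<0.05; 30 per group cannot support a verdict on recurrence or on no difference between the two technologies

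*Protocol*

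**What the plan says.** The Sample Size section of the Protocol notes that there are no local timing data for bidirectional block. It then relies on prior publications, citing a pilot-study recommendation, to conclude that "a sample size of 120 patients is sufficient for this feasibility study i.e. 30 patients in each group". This is the only justification given for the size.

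The rest of the document describes a comparative trial:

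- **Hypotheses.** Hypothesis 1 is that contact force or ECI sensing "will result in lower procedure time, reduced RF requirements and improved outcomes compared to the conventional approach". Hypothesis 2 is that "There would be no difference in outcome measures between contact and ECI".
- **Study Design.** The purpose is given as "In order to examine these hypotheses we aim to perform a multicentre prospective, randomised study".
- **Outcome measures.** The primary outcome is time to bidirectional block, followed by total RF time and energy. Secondary outcomes cover complications, re-conduction, procedure and fluoroscopy time, radiation, cost and long-term success.
- **Statistical methods.** Continuous variables are reported as mean ± SD or median and IQR, and categorical variables are compared by a chi-squared test. The decision rule is "A p value <0.05 will be considered statistically significant".
- **Expected value of results.** What is unclear is "whether the individual differences between contact technologies offer specific clinical advantages, and this trial will provide insight into this". A later definitive trial is not mentioned.

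**The concern.** The number of patients is justified for one kind of study, while the hypotheses and the decision rule belong to another. A feasibility rationale can support 30 per group without a power calculation, because such a study is not expected to settle comparative questions. This protocol asks it to settle two, and gives a significance threshold as the means of doing so.

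The harm lies in how a null result would be handled. Under the p<0.05 rule, a non-significant difference in six-month recurrence counts against hypothesis 1, and a non-significant difference between contact force and ECI appears to confirm hypothesis 2. If the size makes non-significance likely whatever the truth, neither conclusion is earned. The label, hypotheses, outcomes and sample size are all fixed in the protocol, so a separate analysis plan would not remove the mismatch.

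**Working it through.** **1. The plan's own figure.** 120 / 30 = 4 groups, so the arithmetic is consistent. The 30 per group cannot be reproduced from a power or precision formula, because no effect size, SD, power or interval width is stated.

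**2. Inputs.**
- 30 per group (Sample Size).
- Threshold 0.05 (Statistical methods), taken as two-sided because no side is stated.
- Control recurrence 5-10% (Background, section on catheter ablation of atrial flutter).
- Assumed: sensing halves recurrence.
- Assumed: the two sensing groups are pooled against the two control groups, giving 60 v 60. This is the most favourable comparison.

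**3. Power for recurrence.** The test is the specified chi-squared test without continuity correction. Power is obtained by enumerating every pair of event counts (a, b) and summing the binomial probabilities of the pairs with |a − b|/n ÷ √[p̄(1 − p̄)·2/n] > 1.96, where p̄ = (a + b)/(2n).

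| True rates | 30 v 30 | 60 v 60 |
|---|---|---|
| 10% v 5% | 10.6% | 17.4% |
| 5% v 2.5% | 3.1% | 9.3% |
| 10% v 0% (limiting case) | 35.3% | 86.3% |

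Of these scenarios, only complete abolition of a 10% recurrence rate, with pooled groups, passes 80%.

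For scale, the usual formula n = [1.96√(2p̄(1 − p̄)) + 0.842√(p1(1 − p1) + p2(1 − p2))]² / (p1 − p2)², with p̄ the mean of p1 and p2, gives these sizes for 80% power:
- 10% v 5%: (0.730 + 0.312)² / 0.0025, or 435 per group.
- 5% v 2.5%: (0.527 + 0.226)² / 0.000625, or 906 per group.

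**4. Precision for recurrence at 60 v 60.** Half-width = 1.96√[(p1(1 − p1) + p2(1 − p2))/60].
- 10% v 5%: 1.96√(0.1375/60) = 9.4 percentage points, against a true difference of 5.
- 5% v 2.5%: 1.96√(0.0719/60) = 6.8 points, against a true difference of 2.5.

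**5. Continuous outcomes (time to block, RF time), in SD units.** The 95% CI half-width is t × √(2/n), and the effect detectable with 80% power (normal approximation) is (1.96 + 0.842)√(2/n).

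| | 30 v 30 | 60 v 60 |
|---|---|---|
| CI half-width | 2.002 × 0.258 = 0.52 SD | 1.980 × 0.183 = 0.36 SD |
| Detectable with 80% power | 0.72 SD | 0.51 SD |
| Power for 0.5 SD | 49% | 78% |

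**6. Hypothesis 2.** Contact force v ECI among the sensing groups is a 30 v 30 comparison. If the two observed means were identical, the interval would still run about 0.52 SD either way. If both groups had 10% recurrence, the half-width would be 1.96√(2 × 0.09/30) = 15 points; at 5% it would be 1.96√(2 × 0.0475/30) = 11 points. With no margin stated, nothing in the protocol says which of these differences would be small enough to ignore.

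**The case against.** **Secondary outcomes need not be powered, and a pilot may run comparative tests.** Both are true. Long-term success is a secondary outcome, and low power for it would not by itself be a defect. The point survives because hypothesis 1 includes improvement in outcomes, Study Design says the trial examines that hypothesis, and Statistical methods applies one threshold throughout.

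**Outcomes in hypothesis 1 is not defined.** This also stands. The word could cover complications, re-conduction or fluoroscopy time as well as recurrence. The power figures above therefore speak only to the recurrence part.

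**Estimates and intervals could be left to the analysis plan.** In part. How results are tabulated can be left there. Whether the trial's conclusions are confirmatory or exploratory follows from the hypotheses, the size and the decision rule, all of which the protocol fixes.

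Three stronger readings are tempting, and the documents do not support them:

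- *The trial will leave nothing for a later study except p values.* Statistical methods already plans mean ± SD or median and IQR, and re-conduction and long-term success are named outcomes. What is missing is a statement that these will serve to size a later trial.
- *The trial can test none of hypothesis 1.* At 60 v 60 there is 78% power for a 0.5 SD difference in a continuous outcome, so the procedural parts are testable if the effect is moderate to large.
- *Even a clear split in recurrence would miss significance.* That depends on a more conservative test, such as Fisher's exact test. The protocol names chi-squared, which is why the working uses it.

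**Conclusion.** The inconsistency is in the text. The size is described as "sufficient for this feasibility study" and has no other basis, while the trial is set up to reach verdicts on two comparative hypotheses at p<0.05. Under the assumed halving of recurrence, power is about 17% (10% v 5%) or 9% (5% v 2.5%) with the favourable 60 v 60 pooling, and about 11% or 3% at 30 v 30. The 95% intervals at 60 v 60, about 9 and 7 points either way, are wider than the differences sought. Hypothesis 2 cannot be established by non-significance at this size without a margin.

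These figures rest on the protocol's 5-10% recurrence applying to the control groups, a halving by sensing, a two-sided uncorrected chi-squared test and, for 60 v 60, a pooling the protocol does not state. The conclusion is limited to the recurrence part of hypothesis 1 and to hypothesis 2. It does not extend to large effects on procedure or RF time, and it does not mean that the trial must be enlarged. The change should be made because it alters what the trial may legitimately conclude; patient safety is not affected.

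**What to change.** Amend the wording in three sections and leave the design as it is:

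1. **Hypotheses and Sample Size:** state that all comparisons are exploratory, and that the SDs of time to block and RF time and the re-conduction and six-month recurrence rates, which are already planned, will be reported for sizing a later trial.
2. **Statistical methods:** make between-group estimates with 95% confidence intervals the basis for conclusions in place of the p<0.05 verdict. Report six-month success as rates with intervals, without a claim of improvement.
3. **Hypothesis 2:** state that a non-significant contact force v ECI comparison will not be read as showing no difference, and report the interval instead.

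The cost is an amendment to the text. No patients, visits or measurements are added. The trial gives up a confirmatory claim for hypotheses 1 and 2, which its stated feasibility rationale does not support in any case.

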### Statistical methods

Continuous variables will be checked for normality. If they are normally distributed the results will be expressed as mean  $\pm$  SD and compared by Student's t-test or ANOVA. If they are skewed the results will be expressed as median and interquartile range, and compared using the Mann Whitney U test. A chi-squared test will be used to compare categorical variables. A p value <0.05 will be considered statistically significant. Alternative statistical methods and additional analyses will be conducted as deemed appropriate.

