### Patient preparation and procedure.

As per standard practice, oral anticoagulation will be administered to the majority of patients who will then go on to have the procedure performed with uninterrupted warfarin (INR 2-3.5). Depending on randomisation, either the Ensite or CARTO-3 mapping system will be used, and the respective reference patches will be applied to the patient in the cardiac catheter laboratory. Venous sheaths will be inserted into the right and/or left femoral veins. A decapolar catheter will be inserted into the coronary sinus, and a quadripolar catheter into the right ventricle. An additional 20 pole Halo diagnostic catheter (Biosense Webster, Diamond Bar CA, US) can be placed around the tricuspid valve annulus as per operator preference. The creation of three dimensional right atrial geometry will be left to the discretion of the operator and is not a requirement.

A flutter line will be created by either a drag approach or point by point ablation using an irrigated tip Thermocool Smart Touch (Biosense Webster, Diamond Bar CA, US), or an Ensite Verisense catheter (St Jude Medical, St Paul MN, US). In the control group the operator will be blinded to contact force or ECI, by closing the respective sensing information windows on the 3D mapping system. Energy will be delivered at each point for a minimum of 30 seconds with flow limited to 17ml/min and power limited to 40W with a maximum temperature of 48°C. If bidirectional block is not achieved on the first pass, additional ablation targeting gaps will be applied. Following bidirectional block, a waiting time of 30minutes will be observed to check for, and react to, isthmus re-conduction. The procedure will end at this stage.

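### If procedural cost is skewed, the protocol's general rule replaces mean cost with a median and a Mann Whitney test, neither of which tests or estimates a difference in mean cost

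*Protocol*

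**What the plan says.** Outcome measures in the protocol lists cost among the secondary outcomes: "total procedure time, procedural cost, fluoroscopy time". It gives no costing method, no unit costs and no analysis particular to cost.

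Statistical methods then sets one sequence for all continuous data. It opens with "Continuous variables will be checked for normality". Normally distributed variables are summarised by mean and SD and "compared by Student's t-test or ANOVA". For the rest: "If they are skewed the results will be expressed as median and interquartile range, and compared using the Mann Whitney U test". The threshold is "A p value <0.05 will be considered statistically significant", and the section ends with "Alternative statistical methods and additional analyses will be conducted as deemed appropriate".

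Sample Size plans 120 patients, 30 in each group, and calls the trial a feasibility study.

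**The concern.** A cost comparison is normally read as an answer to one question: what would it cost, on average, to treat patients one way rather than another? The total for a group is the number of patients times the mean. A median cannot be scaled up in that way.

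Mann Whitney asks whether values in one arm tend to be larger than those in the other. This matches a question about means only when the two distributions have the same shape and differ by a shift. If one arm has a heavier right tail, ranks and means can part company. The trial could then report a significant cost difference when mean costs are equal, or no difference when the means differ. On the skewed branch the rule provides neither a mean cost difference nor an interval for one.

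The protocol itself fixes both the summary and the test for skewed variables, so this is not simply detail left to an analysis plan that is not shown.

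**Working it through.** **1. Figures in the protocol.** Four groups of 30 give 4 × 30 = 120, as stated in Sample Size. Funding asks for £300 per catheter plus £100 administration per patient: 120 × (300 + 100) = £48,000, as stated. No mean, SD, effect size or power is given for cost, so there is no planned figure to reproduce for it. Everything below rests on assumed distributions and a two-sided 5% test.

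**2. Why ranks and means part company (lognormal cost, arbitrary units).** Let log cost be normal with SD s. Then mean = median × exp(s²/2), and the probability that a patient in arm 1 costs more than one in arm 2 is Φ((μ1 − μ2)/√(s1² + s2²)), where μ is the log median. Mann Whitney responds to how far this probability lies from 0.5.

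Set both means to 3000, with s1 = 0.3 and s2 = 1.0:
- Medians: 3000 × exp(−0.045) = 2868 and 3000 × exp(−0.5) = 1820.
- μ1 − μ2 = (1.00 − 0.09)/2 = 0.455, and √(0.09 + 1.00) = 1.044.
- Probability: Φ(0.455/1.044) = Φ(0.436) = 0.67, not 0.5, although the means are equal.
- Expected total for 30 patients: 30 × 3000 = 90,000 in both arms. Scaling the medians would give 30 × 2868 = 86,040 and 30 × 1820 = 54,600.

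**3. Rejection rates with equal means, lognormal (10,000 simulated trials each).**

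| log-SD | Mann Whitney, 30 v 30 | Welch, 30 v 30 | Mann Whitney, 60 v 60 | Welch, 60 v 60 |
|---|---|---|---|---|
| 0.3 v 0.3 (identical) | 4.9% | 4.9% | 4.8% | 4.7% |
| 0.3 v 0.6 | 19% | 5.7% | 33% | 5.9% |
| 0.3 v 0.8 | 39% | 7.8% | 66% | 6.6% |
| 0.3 v 1.0 | 61% | 10.6% | 88% | 8.6% |

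The 60 v 60 columns assume that two groups are pooled.

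**4. The opposite failure: equal medians, unequal means.** With both medians at 3000 the probability in step 2 is Φ(0) = 0.5, so Mann Whitney has almost nothing to detect. The first mean is 3000 × exp(0.045) = 3138. The others are 3000 × exp(0.18) = 3592, 3000 × exp(0.32) = 4131 and 3000 × exp(0.5) = 4946. At 30 v 30, Mann Whitney rejects in 5.7%, 6.2% and 6.7% of trials and Welch in 11%, 20% and 28%.

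**5. A second model: routine cases plus some prolonged ones.** Cost is taken as linear in laboratory time, with mean 125 min (the middle of the 100–150 min cited in Sample Size). Routine SD is 10, 15 or 20 min. Between 15% and 30% of control cases and 5% to 10% of sensing cases are prolonged, by 60 to 120 min. All but the 125 min are assumptions. Example: 20% v 10% prolonged by 90 min. For equal means the base times must be 125 − 0.20 × 90 = 107 and 125 − 0.10 × 90 = 116 min. With SD 15, Mann Whitney rejects in 15% of trials at 30 v 30.

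Over the 12 settings at 30 v 30, Mann Whitney rejects in 6% (SD 20, 60-min tail) to 75% (SD 10, 120-min tail). Welch stays near 5%. A re-run of the whole grid with 5,000 trials per setting gave the same picture.

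If base times are equal and only the tail shortens, a true mean saving of 9 to 12 min shows as a median difference of about 1.6 to 8.6 min. Power at 30 v 30 is then about 8% to 26% for Mann Whitney and 13% to 41% for a comparison of means.

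**The case against.** The strongest reply is that the harm is conditional and its size unknown. The problem needs cost to be skewed and the arms to differ in shape. If sensing simply moved every procedure's cost down, Mann Whitney would give the right direction. The high rejection rates under equal means need a worse typical case to offset a lighter tail exactly, and Mann Whitney is then detecting a real difference between distributions. A comparison of means also has low power at 30 per group, and Welch is somewhat anti-conservative under heavy skew. The final sentence of Statistical methods leaves room for other methods, cost is one of several secondary outcomes, and neither hypothesis mentions it.

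All of that stands as a limit on importance. It does not remove the point: the sentence on alternatives names no method and does not commit to reporting mean cost.

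Stronger readings that a reader might infer are not supported:
- **That skew is built into the procedure because most cases finish on the first pass.** Patient preparation and procedure says only "If bidirectional block is not achieved on the first pass, additional ablation targeting gaps will be applied". It gives no proportion. The step makes a right tail possible, but the tail and any benefit concentrated in it are assumptions.
- **That Mann Whitney points the wrong way when mean costs are equal.** With equal means no direction is right. The fault is a significant result that says nothing about the mean.
- **That the £300 catheter cost separates the arms.** If sensing patients alone bore it, an assumed model with equal means gives Mann Whitney rejection in about 99% of trials at 30 v 30. But the control group uses the same catheters with the sensing windows closed, and the £48,000 budget charges £300 for all 120 patients. That scenario does not describe this trial.
- **That the protocol needs a mean for procedure time.** The sentence that sensing "can potentially shorten procedure times allowing more patients to be treated" is motivation in Expected value of results, not a planned estimate of throughput.

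**Conclusion.** The point holds in a limited form. The rule for skewed variables covers procedural cost without exception, and on that branch the trial would neither test nor estimate a difference in mean cost. Whether this misleads depends on cost being skewed and on the arms differing in shape or spread.

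The size cannot be fixed from the protocol. Under the two assumed models with equal means, Mann Whitney rejects in about 6% to 75% of trials at 30 v 30 and a comparison of means in about 5% to 11%. These figures show that the error is possible and can be large; they do not predict its size in this trial. The importance is minor, since cost is a secondary outcome in a feasibility study.

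**What to change.** Exempt procedural cost from the normality check and its Mann Whitney branch with one sentence in Statistical methods. For example: whatever its distribution, procedural cost will be reported as the arithmetic mean per arm and the difference in means with a 95% confidence interval, obtained by non-parametric bootstrap; median and interquartile range will be given as description. Reporting total procedure time in the same way is optional.

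This needs no new patients or data. Its drawback is that at 30 per group the interval will be wide and sensitive to a few very costly cases. It should be read as estimation, not as a decisive test.

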### RISKS AND EXPECTED VALUE OF RESULTS

#### **Potential Risks**

All subjects included in the study will be exposed to the risks of catheter ablation. These include minor risks (spontaneous resolution without treatment) of femoral bruising, chest pain and palpitation. Major risks (require treatment) include procedure failure resulting in recurrent sustained atrial arrhythmia (<5%), pericardial effusion leading to tamponade (<1%), stroke (<1%), femoral vascular complications (1%), and AV node damage requiring pacing (<1%). As subjects will have already been assessed by an expert as clinically indicated to have catheter ablation for AFL these risks are not directly related to the study. All subjects will routinely be informed of these risks and provide written informed consent for the procedure as per standard practice. The techniques and treatment strategies used for the study are identical to standard clinical ablation procedures.

